**13.5 Monitoring****13.5.1 Safety Monitoring****Neoadjuvant treatment completion monitoring:**

To maintain meaningful outcome comparisons between two arms, the completion of neoadjuvant treatment will be monitored. The early off treatment (EOT) rate will be defined as the number of patients who receive fewer than 8 cycles (e.g., 0 to 7 cycles) of neoadjuvant chemotherapy, due to disease progression, death, toxicity, treating physician discretion, and other disease related reasons, after LCRT divided by the number of patients who complete LCRT and start at least one dose of chemotherapy. Patients who withdraw from protocol treatment due to reasons that are not related to disease will be excluded from this analysis.. OPRA trial reported 7% (8/116) of patients who received  $< 8$  cycles of FOLFOX after LCRT in consolidation arm.

We will compare EOT rates between two arms (experimental vs. control arms) when 88 (44 per arm), 174 (87 per arm) and 262 (131 per arm) evaluable patients complete

neoadjuvant chemotherapy or are off neoadjuvant chemotherapy early. Lan-DeMets OF spending function will be used to control multiple comparisons. If the difference in EOT rate (experimental arm minus control arm) is greater than 22.0%, 10.4% and 6.7% (corresponding p-value: < 0.001, 0.016, 0.045) at three time points, respectively, the treatment, toxicity and off treatment reasons data will be thoroughly reviewed and potential protocol modifications, including suggesting halting accrual, will be formulated under the consultations with CTEP. The total sample size of 262 patients will provide 80% power to detect a difference in EOT rate of 10% at a one-sided alpha of 0.05 significance level.

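### The early-off-treatment limits are scaled to 17% versus 7%: they meet the stated 80% power but not the stated one-sided alpha of 0.05, and can disagree with the p-values printed beside them

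*Combined protocol and SAP*

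**What the plan says.** Section 13.5.1 compares the EOT rate between arms "when 88 (44 per arm), 174 (87 per arm) and 262 (131 per arm) evaluable patients complete" or leave neoadjuvant chemotherapy early. It states that "Lan-DeMets OF spending function will be used to control multiple comparisons". The trigger is a difference, experimental minus control, "greater than 22.0%, 10.4% and 6.7% (corresponding p-value: < 0.001, 0.016, 0.045").

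The operating characteristics are given as "80% power to detect a difference in EOT rate of 10% at a one-sided alpha of 0.05 significance level", with 262 patients in total. The only EOT rate cited is for the control regimen: "OPRA trial reported 7% (8/116) of patients who received" fewer than eight cycles of FOLFOX.

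The section does not name the test, the variance behind the limits or the control rate assumed for design. It presents the p-values as corresponding to the differences, without saying which governs if the two part company. Crossing a limit leads to a data review and possible protocol changes, which may include a suggestion to halt accrual, in consultation with CTEP.

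**The concern.** A type I error is a probability computed when the two arms share the same rate. Limits on a raw difference in proportions have a fixed alpha only if that common rate is known, because the standard error depends on it. Here the limits appear to be scaled to the alternative (17% versus 7%), whose standard error is larger than the one at 7% in both arms. The alpha quoted for the rule would then not be a property of the rule.

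The limits and p-values are also printed as if they were one criterion. If they are not equivalent on observed data, the DSMB could see a difference over the limit with a p-value above its level, or the reverse, with no instruction on which to follow. This rule monitors whether the triplet can be completed as often as the doublet, so what counts as a signal should be unambiguous.

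**Working it through.** **Inputs.** All from Section 13.5.1: 44, 87 and 131 patients per arm; Lan-DeMets O'Brien-Fleming-type spending; one-sided alpha 0.05; a 10-point difference; control rate 7% (8/116 = 6.9%). The 7% is an inference: the section cites it but does not call it the design rate.

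**1. Sample size and power.** For 7% versus 17%, one-sided 0.05 and 80% power, the pooled two-proportion formula gives 130 per arm. With 131 per arm the power is 80.4%. The plan's 262 is reproduced, which supports 7% as the design rate.

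**2. Critical values.** At information fractions 44/131 = 0.336, 87/131 = 0.664 and 1, the spending function gives z = 3.187, 2.146 and 1.694, that is p = 0.0007, 0.0159 and 0.0451. The printed p-values are correct spending levels and together spend 0.05.

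**3. Where the limits come from.** Limit = z × SE, with SE = √{[p₁(1−p₁) + p₂(1−p₂)]/n}.

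| Look (n per arm) | SE at 17%/7% | z × SE | Printed limit | p at printed limit, 17%/7% SE | SE at 7%/7% | p at printed limit, 7%/7% SE |
|---|---|---|---|---|---|---|
| 1 (44) | 0.0685 | 21.8% | 22.0% | 0.0007 | 0.0544 | 0.00003 |
| 2 (87) | 0.0487 | 10.4% | 10.4% | 0.016 | 0.0387 | 0.0036 |
| 3 (131) | 0.0397 | 6.7% | 6.7% | 0.046 | 0.0315 | 0.017 |

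For look 3: 0.067/0.0397 = 1.69 on the alternative variance, against 0.067/0.0315 = 2.13 on the null variance at 7%.

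**4. Overall type I error of the printed limits.** This is the chance that the difference exceeds its limit at any look when both arms share one rate. Binomial simulation, 1,000,000 trials per row:

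| Common rate | Printed difference limits | Pooled z-test at the spending levels |
|---|---|---|
| 5% | 0.008 | 0.053 |
| 7% | 0.020 | 0.051 |
| 10% | 0.042 | 0.051 |
| 12% | 0.056 | 0.050 |
| 15% | 0.076 | 0.050 |

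A multivariate normal calculation gives 0.018 at 7% and places the crossing of 0.05 near 11.5%.

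**5. Power.** At 7% versus 17% the printed limits give 0.804 (normal) or about 0.815 (simulation). The pooled z-test gives 0.81.

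**6. Do the two printed criteria agree on data?** With an observed control rate of 7% and the pooled test:

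- Look 1: a 22.0-point difference has p = 0.0036. The 0.0007 level needs about 27.6 points, so the difference limit is met first. Example: 3/44 versus 13/44 is 22.7 points, with z = 0.227/0.0822 = 2.76 and p = 0.003.
- Look 2: 10.4 points has p = 0.018; the 0.016 level needs about 10.7 points. The two nearly coincide.
- Look 3: 6.7 points has p = 0.038; the 0.045 level is reached at about 6.3 points, so the p-value is met first. Example: 7/131 versus 15/131 is 6.1 points, with z = 0.0611/0.0343 = 1.78 and p = 0.037.

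With true rates of 7% and 17%, and all three looks evaluated, the two criteria disagree at one or more looks in about 12% of simulated trials.

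**The case against.** The strongest defence is that this is a convention, not a slip. At the 17%/7% variance the limits and p-values agree to rounding. Section 13 does the same elsewhere: the 9.3% final phase II limit gives z = 1.648 with the unpooled 67%/50% variance, and the 0.114 regrowth limit gives z = 1.642 at 42%/22%. That stands. A reader might infer from the null-variance column that the printed p-values are arithmetically wrong, and the documents do not support that. What is missing is a statement of the variance, and the alpha that follows from it.

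A reader might also infer that the rule protects patients less than claimed. That does not follow either. The stated power for a 10-point excess is met, and a type I error of 0.02 at 7% means fewer needless reviews, not missed signals at the design alternative. The direction is not uniform: above a common rate of about 11.5% the limits alarm more often than 0.05, and at look 1 the difference limit is easier to cross than the p-value level.

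Two further points have weight. The 0.02 depends on both arms being at 7%; at 10% the alpha is close to nominal. And crossing leads only to a review, alongside the grade 4 or higher non-hematologic adverse event rule, monthly review by the study chair and statistician, and six-monthly DSMB reports. These lower the severity. They do not make the stated alpha correct at the one rate that the section cites, and they do not say which criterion governs.

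**Conclusion.** The point holds in a limited form. The limits of 22.0%, 10.4% and 6.7% are calibrated to the design alternative. They meet the stated power but not the stated one-sided alpha of 0.05, which is about 0.02 at 7% in both arms and depends on a common rate that is unknown in advance. Section 1.3 says that OPRA ran at sixteen highly specialized centers and that this trial seeks a broader range of sites, so a control rate other than 7% is plausible. The differences and a pooled-test p-value are two different rules that can conflict on realistic counts, and the text does not rank them.

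This rests on 7% as the design control rate (inferred, but it reproduces the sample size, the power and all three limits), on looks at exactly the planned numbers, and on the pooled test as the reading of the unnamed test. Severity is low: the consequence of crossing is a review with CTEP.

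**What to change.** In Section 13.5.1, make the binding trigger the one-sided p-value of the pooled difference-of-proportions test at the spending-function levels, about 0.0007, 0.016 and 0.045. State 7% as the assumed control rate, and describe 22.0%, 10.4% and 6.7% as approximate differences at 17% versus 7%. Sample size and looks stay as they are. Alpha is then about 0.05 at common rates from 5% to 15%, with power about 0.81 at 7% versus 17%.

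The cost should be disclosed. At 7% versus 17% the chance of firing at look 1 falls from about 0.046 to about 0.02. If rates are higher, power falls: at 10% versus 20% it is 0.73 instead of 0.80.

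If the team values the early sensitivity and keeps the fixed differences as the trigger, it should say that they govern and restate the alpha as about 0.02 at 7% in both arms, with its range over common rates.

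Recomputing the differences on the 7%/7% variance (about 17.3%, 8.3% and 5.3%) is not a remedy. Those limits give an alpha of 0.060 at a common 7% and 0.145 at 15%, so they overshoot 0.05 and still depend on the unknown rate.

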**R0 resection for patients on WW strategy monitoring:**

We will carefully monitor the R0 resection rate among patients who proceed to a WW strategy after TNT and later require TME during follow-up. Patients enrolled on two arms will be pooled for this monitoring. OPRA reported among 120 (out of 166 enrolled) patients in the CRT-CNCT arm who initially entered in the WW strategy, only 33 patients developed tumor regrowth. Four patients had local excision rather than TME and none required further treatment. Another four patients in the CRT-CNCT group recommended for TME declined any additional treatment. Three patients were not able to undergo TME due to progressive disease. Therefore, only 22 patients (~13 to 15 % of enrolled patients) underwent TME on WW protocol. We estimate approximately 46 patients pooling two arms will have TME on WW following cCR deemed after TNT.

We consider a true R0 rate of 94% or higher (alternative hypothesis) to be adequate and 83% or lower (null hypothesis) to be inadequate. The following monitoring rules will provide 85.1% power to test the hypothesis whether the R0 resection rate in this small population is adequate, at a one-sided alpha of 0.086, with 56.6% likelihood of rejection at the first stage of 23 patients:

- When the first 23 patients who undergo TME on WW protocol had R0 resection data available, if 19 or fewer patients have R0 resection, OR
- when the first 46 who undergo TME on WW protocol had R0 resection data available, if 41 or fewer patients have R0 resection

then the treatment, toxicity and disease evaluation data will be thoroughly reviewed and potential protocol modifications, including suggesting halting accrual, will be formulated under the consultations with CTEP.

**Tumor regrowth for patients on WW strategy monitoring:**

We will carefully monitor the incidence of tumor regrowth among patients who proceed to a WW strategy after completion of pre-operative TNT. The OPRA trial reported a regrowth rate of 22% (95% CI, 14-29%, unpublished data) for patients randomized to CRT-CNCT who underwent the WW strategy, at one year of follow-up after completion of pre-operative TNT.

**Rule # 1: Comparing 1-year tumor regrowth rates between two arms.**

The analysis population of this monitoring rule is defined as patients who are included in the phase II portion final analysis AND achieve cCR status and choose WW strategy after completion of pre-operative TNT. The one-year regrowth rate will be defined as number of patients who experience tumor regrowth (regardless of whether it can be salvaged by TME) within one year after the last dose of pre-operative TNT divided by the total number of patients in the analysis population. The one-year regrowth rate will be estimated within each arm separately, when all patients in this population are followed for at least one year after last dose of chemotherapy. Based on Phase II design assumptions, the sample sizes

will be approximately 93 ( $=156 \times 0.593$ , critical value to reject phase II null hypothesis) and 78 ( $=156 \times 0.5$ , phase II control arm assumption) patients in Arm A and B, respectively.

DFS comparison between two arms will be noted to be concerning if the one-year regrowth rate in triplet TNT arm (Arm A) is much higher than that in the doublet TNT arm (Arm B). Thus, if:

- The difference in one-year regrowth rates (i.e., triplets arm minus doublets arm) is  $> 0.114$ , then the further accrual will be halted after discussion with CTEP.

This monitoring rule will provide 89% power to test the hypothesis that one-year regrowth rate in the triplet TNT arm (Arm A) is 42% versus that in the doublet TNT arm (Arm B) is 22%, i.e., 20% higher than that in doublet arm, at a one-sided alpha of 0.05.

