**Rule # 2: Comparing overall 1-year tumor regrowth rate (pooling two arms) to historical rate.**

The goal of this rule is to guard against an excessive regrowth rate that may be seen across the various NCTN sites. The International W & W Database [48] reported a 15.5% 1-year regrowth rate. However, the patients included in this retrospective database were not treated with TNT and cCR was determined by various and heterogeneous methods. It should be noted that these patients are taken from highly selected institutional case series, there is no denominator, non-uniform definitions of response, relatively short clinical follow-up, inconsistent surveillance protocols and variable patient selection criteria and neoadjuvant treatment regimens. The 1-year regrowth rate from this population is very likely a underestimation and may not be compatible with the setting of a modern clinical trial. Therefore, relying on prospectively collected data with uniform selection criteria and surveillance strategies similar to our trial, we can take into account the OPRA data. The OPRA data does have the limitation of therapy provided at primarily tertiary centers, but does provide the advantage of a prospective cohort of patients treated with TNT and subsequently followed in a manner identical to what we have described for the Janus Rectal Cancer Trial. Therefore, we consider a 1-year rate of local regrowth of 22% observed from OPRA trial as the “upper limit” of safety benchmark, i.e., it is considered not safe for patients if the 1-year rate of local regrowth in JANUS trial is larger than this benchmark.

The same population (i.e., assuming total of 171 NOM patients) and definition of 1-year tumor regrowth rate in Rule #1 will be applied to Rule #2. We consider a true 1-year regrowth rate of 32% or higher (alternative hypothesis) to be unacceptable and 22% or lower to be acceptable. If the observed 1-year regrowth rate is  $> 28.2\%$  (observed 6.2% increase), then the further accrual will be halted after discussion with CTEP. This monitoring rule will provide 85.6% power to detect if the true 1-year regrowth rate is unacceptable, i.e. 10% higher than historical rate of 22%, at a one-sided alpha of 0.025.

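### The one-year regrowth rate behind both accrual-halting rules has no handling for patients lost before one year; taken literally it is biased down, which matters mainly for Rule #2

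*Combined protocol and SAP*

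**What the plan says.** Section 13.5.1 has two rules on tumor regrowth in patients who reach cCR and choose watch and wait (WW).

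- **Definition (Rule #1).** The rate is the number of patients with regrowth "within one year after the last dose of pre-operative TNT divided by the total number of patients in the analysis population".
- **Timing (Rule #1).** It is estimated in each arm "when all patients in this population are followed for at least one year after last dose of chemotherapy".
- **Rule #1 design.** Sample sizes "will be approximately 93" in Arm A and 78 in Arm B. If the triplet rate exceeds the doublet rate by more than 0.114, "then the further accrual will be halted after discussion with CTEP". The stated power is 89% for 42% against 22%, at one-sided alpha 0.05.
- **Rule #2 design.** The population and "definition of 1-year tumor regrowth rate in Rule #1 will be applied to Rule #2". The arms are pooled (171 patients), 22% is acceptable, 32% is unacceptable, and the limit is an observed rate above 28.2%. On power: "This monitoring rule will provide 85.6% power to detect if the true 1-year regrowth rate is unacceptable", at one-sided alpha 0.025.

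Neither rule says how to treat a WW patient who is lost, withdraws or dies without regrowth before one year, and no loss rate is assumed. Other parts of Section 13 do address such cases. The early-off-treatment rule excludes withdrawals unrelated to disease, the R0 rule counts patients whose resection data are available, the phase II interim look requires known cCR status, and Section 13.4.3 plans Kaplan-Meier estimates for secondary time-to-event endpoints.

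**The concern.** A patient who leaves surveillance at month 6 without regrowth contributes half a year of information. Under the stated ratio the same patient can never enter the numerator but stays in the denominator. The estimate is then too low, and too low is the unsafe direction for a rule meant to detect excess regrowth.

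The timing condition does not settle the matter. It presumes complete follow-up but does not say what to do if one patient is lost. Across 171 patients that is likely: at a 1% risk each (an assumption), the chance of at least one loss is 1 − 0.99^171 = 82%. The analyst must then count such patients as non-events, drop them, or censor them. That choice would be made with the data in view, on a result that can halt accrual.

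Death without regrowth is a lesser issue. If it is treated as a competing event, keeping the patient in the denominator is correct, but the plan should say so. The bias comes from loss and withdrawal.

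**Working it through.** **Inputs from Section 13.5.1.** Rule #1: 93 and 78 patients, 42% against 22%, limit 0.114. Rule #2: 171 patients, 22% against 32%, limit 28.2%.

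**Step 1. Reproduce the stated figures (no loss).**

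- Rule #2 limit: 0.22 + 1.96 × √(0.22 × 0.78 / 171) = 0.22 + 1.96 × 0.0317 = 0.282.
- Rule #2 power, normal: Φ((0.32 − 0.282) / √(0.32 × 0.68 / 171)) = Φ(0.038 / 0.0357) = 85.7%, against 85.6% stated (85.6% with the unrounded limit).
- Rule #2, exact binomial: 0.282 × 171 = 48.2, so a halt needs 49 or more regrowths. Power is 84.6% and false-halt probability 2.5%.
- Rule #1: standard error √(0.42 × 0.58 / 93 + 0.22 × 0.78 / 78) = 0.0694; limit 1.645 × 0.0694 = 0.114; power 89.2% normal and 89.0% exact, against 89% stated.

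Both stated powers are right if no patient is lost.

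**Step 2. Model the loss.** Let f be the share lost before one year and g the share of their first-year regrowths that goes unseen. Then:

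expected crude rate = true rate × (1 − f × g)

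The documents give neither f nor g. Regrowth times are assumed uniform from 0.2 to 1 year after the last dose, since cCR is first assessed 8-12 weeks after TNT. If losses are uniform over the same window, g = 0.5. If they are uniform over the whole year, g = 0.6, the mean regrowth time.

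**Step 3. Rule #2 at a true rate of 32%, exact (49 or more of 171).**

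| Loss f | Crude rate, g = 0.5 / 0.6 | Power, g = 0.5 / 0.6 |
|---|---|---|
| 0% | 32.0% | 84.6% |
| 1% | 31.8% / 31.8% | 83.5% / 83.3% |
| 2% | 31.7% / 31.6% | 82.4% / 81.9% |
| 5% | 31.2% / 31.0% | 78.7% / 77.4% |
| 10% | 30.4% / 30.1% | 71.6% / 68.5% |

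At 5% loss the bias is only 0.8-1.0 point, but the margin between 32% and the limit is 3.8 points, so a small bias costs several points of power. In the worst case, where every regrowth among lost patients goes unseen (g = 1), power is 71.6% at 5% loss.

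**Step 4. Rule #1 at 42% against 22%, exact enumeration.**

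- Equal loss: 89.0% with none, 87.8% / 87.5% at 5%, 86.4% / 85.9% at 10% (g = 0.5 / 0.6). Both arms shrink together, so the difference changes little.
- 12% lost in the triplet arm and 4% in control, g = 0.6: expected rates 39.0% and 21.5%, power 81%.
- The reverse split: expected rates 41.0% and 20.4%, power 91%.

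**Step 5. Effect of censoring.** Simulated one-year Kaplan-Meier estimates against the same limits (20,000 replicates, exponential times, no competing deaths, loss unrelated to regrowth) give Rule #2 power of about 85% at 5% and 10% loss. The false-halt rate at 22% is 2.9% and 3.3%, against 2.6% with no loss in the same simulation. Rule #1 stays near 89%.

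**The case against.** The strongest reply is that the plan presumes complete follow-up. A reader might infer that it counts lost patients as regrowth-free. It does not say that; this is what the stated ratio does if applied literally, and dropping such patients would also be possible. What stands is that a foreseeable contingency is not addressed.

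A reader might also infer that both halting rules lose much of their stated power. The documents do not support that for Rule #1. Equal loss costs it one or two points at 5%, and nothing in the documents suggests that loss will differ by arm or in which direction.

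For Rule #2, the size rests wholly on an assumed loss rate. WW surveillance is every three months in the first two years (Section 5.0), and Section 12.4 requires endpoint follow-up after therapy stops, so loss may be low. At 1-2% evenly spread loss the cost is about 1-3 points. About one further point of the gap to the stated 85.6% is only normal against exact calculation.

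Two more points have force. The 22% benchmark is cited as unpublished data from the earlier organ-preservation trial, and the documents do not say whether it is crude or Kaplan-Meier, so changing the estimator could create a mismatch with it. The rules are also not the only safeguard: a halt follows discussion with CTEP, the study team reviews safety monthly, and the DSMB reports every six months. None of this tells the analyst what to do with a patient who is lost.

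**Conclusion.** The point holds as a gap in the definition, with a known direction of bias if the text is followed literally. Rule #2 is the sensitive rule: exact power at 32% falls from 84.6% to about 82% at 2% loss, 77-79% at 5% and 68-72% at 10%. These figures assume 171 patients, evenly spread loss unrelated to regrowth, and loss rates that the documents do not supply. Rule #1 is little affected under equal loss, and unequal loss can move it down or up (about 81% or 91% for a 12%/4% split). The documents do not support saying that Rule #2 must fall materially short of its stated power, since that depends on loss not yet observed. The change is still worth making, because the method is standard and the choice should be fixed before the data are seen.

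**What to change.** In Section 13.5.1, for both rules:

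1. Define the one-year regrowth rate as the one-year cumulative incidence from the last TNT dose. Censor patients without regrowth at their last regrowth assessment, and treat death without regrowth as a competing event.
2. Trigger the look when every patient in the population is at least 12 months past the last dose, so that one lost patient cannot block it.
3. Re-check the 28.2% limit under the new estimator, because the false-halt rate rises to about 3% against the stated 2.5%.
4. Confirm whether the 22% benchmark is a crude or a Kaplan-Meier estimate, and state it.

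The cost is a few sentences, standard software and a short recalculation of the Rule #2 limit. No treatment, visit or sample size changes. The drawback is a slightly higher false-halt rate if the limit is left where it is.

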## 13.2 Sample Size

We anticipate enrolling a maximum of 760 patients (380 per arm). We anticipate an accrual rate of 180 patients per year (15 per month) based on similarly accruing studies of Alliance N1048 trial, NRG-GI002, and the OPRA trial. The total accrual period of this study is estimated to be 4.2 years, including start-up time.

For phase II portion, per study design, total of 296 evaluable patients (148 per arm) will be needed to evaluate the primary endpoint. Up to an additional 16 patients (5% inflation) might be accrued to account for cancellation after randomization and major violations. Thus, the total targeted accrual for phase II portion will be up to 312 patients.

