## 13.3 Power Justification

The design of this trial is a randomized, seamless phase II/III trial. After a patient is registered, they will be assigned to one of the two treatment arms in a 1:1 ratio utilizing a dynamic allocation algorithm based on the methods by Pocock and Simon [46].

The patients included in the phase II endpoints analyses will be included in the phase III endpoints analyses. The accrual will not be halted while waiting for phase II endpoints to be matured and analyzed, unless we experience unexpected rapid accrual and/or unacceptably high treatment toxicity, or other unforeseen situations. If the criteria for continuation have been satisfied at conclusion of phase II portion, to protect the phase III comparison, the actual results of the phase II portion will not be released beyond the Alliance DSMB.

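### Regrowth Rules #1 and #2 look once, at about month 38–40, when halting accrual can spare only about 165–195 of 760 patients, and set no regrowth limit for patients enrolled after phase II

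*Combined protocol and SAP*

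**What the plan says.** Rule #1 (Section 13.5.1) compares one-year regrowth between arms. Its population is restricted: "The analysis population of this monitoring rule is defined as patients who are included in the phase II portion final analysis", and of those only patients who reach cCR and choose WW. The plan expects about 93 and 78 such patients. There is one evaluation: "The one-year regrowth rate will be estimated within each arm separately, when all patients in this population are followed for at least one year" after the last chemotherapy dose. The trigger is a difference (triplet minus doublet) above 0.114.

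Rule #2 applies the same population and definition, pooled (171 patients), against OPRA's 22%, which the plan treats as the upper limit of its safety benchmark. The trigger is an observed rate above 28.2%. Both rules end in the same action: "then the further accrual will be halted after discussion with CTEP".

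The accrual clock is in Section 13.2: "We anticipate enrolling a maximum of 760 patients (380 per arm"), "We anticipate an accrual rate of 180 patients per year (15 per month"), and "The total accrual period of this study is estimated to be 4.2 years, including start-up time". For phase II, "the total targeted accrual for phase II portion will be up to 312 patients". Section 13.3 states "The accrual will not be halted while waiting for phase II endpoints to be matured and analyzed", with exceptions for unexpectedly rapid accrual, unacceptably high toxicity or other unforeseen situations.

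**The concern.** Rule #2 is there to guard against excessive regrowth across the network's sites, which are more varied than the specialised centres that ran OPRA. A rule whose only action is to stop accrual protects patients not yet enrolled, so its value depends on how many remain when it is read. Here it is read once, after the last phase II patient has completed neoadjuvant therapy and a further year, while accrual runs on towards 760.

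Patients enrolled after phase II are more than half of the trial, and neither rule includes them. If regrowth were unacceptable, the formal signal would come late; if it worsened as more sites joined, no numeric limit would pick that up.

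**Working it through.** **The plan's own figures.**
- Accrual: 760/180 = 4.22 years (50.7 months), matching the stated 4.2 years.
- Rule #1, 93 vs 78 patients, 42% vs 22%, cut-off 0.114: exact power 0.890 (stated 89%).
- Rule #2, n = 171, one-sided 0.025: limit 0.22 + 1.96 × √(0.22 × 0.78/171) = 28.2%; normal power 0.856 (stated 85.6%). The exact rule, 49 or more of 171, has error 0.0248 and power 0.846.

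**Timing of the look.** The 312th patient enters at 312/15 = 20.8 months. The time from registration to last dose is not given as one figure, so it is an assumption. Start of treatment takes 0–4 weeks, chemoradiation 5–6, the gap 2–4, and chemotherapy to last dose 14–16. The sum is 21–30 weeks, taken as 4.9–7 months with 6 as base.

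Month of look = 20.8 + time to last dose + 12; enrolled = 15 × month.

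| Months to last dose | Look (month) | Enrolled | % of 760 | Remaining |
|---|---|---|---|---|
| 4.9 | 37.7 | 566 | 74.4 | 194 |
| 6 | 38.8 | 582 | 76.6 | 178 |
| 7 | 39.8 | 597 | 78.6 | 163 |

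Each month of data cleaning adds about 2 percentage points. With 6 months to last dose, accrual of 10, 12 or 20 per month gives 65%, 69% or 88%.

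**Who is on WW by then.** Assume restaging at about 8.5 months from registration. Patients past restaging: (38.8 − 8.5) × 15 ≈ 455 of 760 (60%). At the plan's WW fraction of 171/312 (55%), about 250 are on WW, against 171 in the rule.

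**Coverage.** 760 − 312 = 448 patients (59%) are outside both rules; 448 × 171/312 ≈ 246 are expected on WW.

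**An added look at half the cohort.** The first 156 patients give about 85 on WW. The look falls at 156/15 + 6 + 12 = 28.4 months, with 426 enrolled (56%) and 334 remaining. Lan-DeMets O'Brien-Fleming spending at half information gives:
- Rule #2 (one-sided 0.025): early z = 2.96, final z = 1.97. Early limit 0.22 + 2.963 × √(0.22 × 0.78/85) = 35.3%, that is 31 or more of 85. The final limit stays at 28.2%.
- Rule #1 (one-sided 0.05), about 46 vs 39 patients: early z = 2.54, final z = 1.66. The early limit is a difference of about 0.23 (variance at 22%) to 0.26 (variance at the pooled alternative).

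Exact chance that Rule #2 triggers early:

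| True one-year rate | 22% | 32% | 36% | 40% |
|---|---|---|---|---|
| Early trigger | 0.2% | 22% | 50% | 78% |

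For Rule #1 at 42% vs 22% the early trigger probability is about 27–38% (normal approximation), depending on the limit used. With 31/85 early and 49/171 final, Rule #2's exact overall error is 0.0253 (against 0.0248) and its power 84.7% (against 84.6%).

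**The case against.** The strongest reply is that the single look is deliberate. Rule #1 refers to the phase II final analysis, sizes one arm from the phase II critical value, and ties its concern to the disease-free survival comparison, the phase III endpoint. A full-cohort look has 85.6–89% power; a half-cohort look has about 22–38% at the same alternatives. This stands in part: the early look cannot replace the existing one. A reader might infer that it would reliably spare the 334 patients then unenrolled. At the plan's own 32% alternative it would do so about one time in five.

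A reader might also infer that the rules are leftovers from the 312-patient trial. The documents do not support that: the wording refers to the phase II portion and to phase III, and in a trial closing at 312 an accrual halt at this point would have had nothing to stop.

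Nor are later WW patients unmonitored. Section 13.5.1 states a general intention to monitor regrowth on WW. The R0 rule has two looks with no phase II restriction. The study chair and statistician review the trial monthly, and the DSMB receives reports every six months. Regrowth that cannot be removed with an R0 resection is a disease-free survival event. All of this stands, but none of it sets a regrowth limit. R0-salvageable regrowth is expressly not a disease-free survival event, and the phase III interim is expected only after full enrolment.

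**Conclusion.** The point holds as a timing and coverage weakness. Both rules look once, at about month 38–40, with about 582 of 760 enrolled (range 74–79%), so their only stated action can spare about 165–195 patients. No regrowth limit applies to the 448 enrolled after phase II.

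A reader might go further and say the rules cannot protect most of the patients they are meant for. That does not follow: the hazard begins on WW, and about 40% of the planned 760 would not yet be past restaging at the look. The comparison of OPRA's 22% at one year with its 27% at three years should not be used to argue for an earlier look either. The three-year denominator and time origin are not stated, and at most the comparison supports a one-year endpoint, which the rules already use.

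The figures assume steady accrual of 15 per month, no use of the exceptions that allow a pause, continuation into phase III, and about 6 months from registration to last dose. Slower accrual softens them.

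**What to change.** In Section 13.5.1, keep the final limits of Rules #1 and #2 and add one earlier look, when about half of the phase II WW patients (about 85) reach one year after the last chemotherapy dose. Use the Lan-DeMets O'Brien-Fleming spending already specified for the early-off-treatment monitor:
- Rule #2: 31 or more regrowths in 85 (above about 35%); final z 1.97.
- Rule #1: z = 2.54, a difference above about 0.23–0.26 depending on the variance used, which the plan should fix in advance; final z 1.66.

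State in the text that this look guards against large excesses only, and give the trigger probabilities above.

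In the six-monthly DSMB reports, add the one-year cumulative incidence of regrowth for all WW patients, including those enrolled after phase II, pooled and by arm, against the same benchmarks.

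The cost is wording in one section, a small amount of alpha spent early and one extra table. Power at the early look is limited. No new visits or data are needed.
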